### Measurement of Stress With the Modified DISE Tool

The DISE is recommended by the National Institute on Aging funded Stress Measurement Network for daily stress measurement. A modified version of the DISE will be administered through the REDCap survey each evening for 2 weeks of the study period. The modified version of the DISE includes questions about the number of times participants felt stressed over the course of the day, their overall stress level, and questions about specific stressor categories (eg, had an argument and had work stress) and how stressful each of those experiences was for the participant. The DISE was modified to allow for direct comparisons between STRIVE and DISE.

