In response to this research gap, we propose to use our novel custom-built Stress Reports in Variable Environments (STRIVE) ecological momentary assessment (EMA) mobile phone app to measure the experience of daily stress of midlife adults in free-living conditions. Using our app to capture data in real time will allow us to determine (1) where and when daily stress occurs for midlife adults, (2) whether midlife adults’ daily stressors are linked to certain elements of the built and natural environment, and (3) how EMA measurement of daily stress is similar to and different from a modified version of the popular Daily Inventory of Stressful Events (DISE) measurement tool that captures end-of-day stress reports (used in the Midlife in the United States [MIDUS] survey) [31].

Completing this study will expand our understanding of mid-life adults’ experience of stress in free-living conditions and pave the way for data-driven individual and community-based intervention designs to promote health and well-being in midlife adults. Potential interventions that could stem from our data include technology-based “just-in-time” interventions that account for spatiotemporal location, mindfulness-based interventions that incorporate environmental stress triggers, and community-based interventions designed to eliminate environmental stressors that are commonly experienced by midlife adults (eg, congested areas).

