### Measurement of Stress With the STRIVE App

Study participants will be asked to carry the researcher’s provided Android mobile phone with them at all times. The STRIVE app passively records the participant’s GPS coordinates every 60 seconds throughout the data collection period (Table 2). Research participants are informed that their location is being tracked by the app. When participants experience a daily stressor, they are asked to open the app and provide a rating of their stress level, a description of the stressor, their preferred coping strategy, and optionally take a photograph of the environment where they experienced stress (Figure 1). Data input is kept to a minimum to reduce participant burden and burnout [33].

**Table 2 table2:** All study measures.

Measurement tools			Measure

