**Real time measurements (all time-stamped)^c^**			
	STRIVE^d^ app	Per 60 second GPS coordinates (continuous) Self-reported stress level (7-point scale) Self-reported stressor (text-based) Self-reported coping response (text-based) Photo of stressful environment (JPEG)	
	Polar Unite Smartwatch	Heart rate (continuous) Activity level (continuous)	
End-of-day recall DISE^e^ measurements^c^			Self-reported overall stress level (7-point scale) Self-reported stressor type Self-reported stress level by stressor (7-point scale) Self-reported date

^a^CDC: Centers for Disease Control and Prevention.

^b^UCLA: University of California, Los Angeles.

^c^Additional measurements include demographics and health history.

^d^STRIVE: Stress Reports in Variable Environments.

^e^DISE: Daily Inventory of Stressful Events.

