### Comparison of STRIVE and DISE Stressor Data

We will compare the number of stressors reported, the type of stressors reported, and the subjective severity of stressors reported by the same individual using the DISE and STRIVE app across 3 time periods. The 3 time periods are designed to differentiate between stand-alone use of each instrument and concurrent use of both instruments, as there is potential for these instruments to be complementary in terms of the scope and depth of data captured. Thematic coding of stressors reported through the DISE and STRIVE app will be conducted to allow for comparison between the two. All stressors will be coded into 7 categories specified by the DISE to retain consistency. Stressful events are categorized into 1 of 7 broad classifications organized by interpersonal tensions, work or education, home, finances, health or accident, network, and miscellaneous. As the unit of analysis of the DISE is the “day,” we will conduct a repeated measures ANOVA to compare the number of stressors reported per day, the average subjective severity of stressors per day, and the type of stressors reported per day across the 3 modes of daily stress reporting, including an interaction of group (STRIVE or DISE) and mode (using only one or both together) to test if there is any effect on the reported stressors by use. A factor will also be included for the order receiving the conditions to account for carryover effects. Models will also be adjusted by demographic variables.

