## Results

This study will take approximately 24 months to complete and will take place between December 2022 and November 2024. Enrollment began in August 2023 and is expected to be completed by July 2024. We expect the following study findings:

A better understanding of where and when stressors occur for midlife adults in free-living conditions. We hypothesize that the quantity of stressors reported, type of stressors reported, and subjective severity of stressors reported by midlife adults will differ by location (eg, at home vs at a park) and time (eg, morning vs evening) throughout the built and natural environment.An understanding of specific elements of the built and natural environment that contribute to midlife adults’ daily stress. We hypothesize that distinct environmental characteristics (eg, abandoned buildings) will emerge as contributors to stress through the qualitative analysis of stressor descriptions and pictures of stressful environments.An understanding of how the STRIVE-based EMA of daily stress is supplementary or complementary to the DISE. We hypothesize that, when reporting through the STRIVE app compared with when reporting through the DISE, midlife adults will report a greater number of daily stressors, a lower average stressor severity, and different types of stressors.

Throughout the study, we will present our research findings at relevant academic or professional conferences and publish peer-reviewed papers. We will also share our study findings with partner governmental organizations and nongovernmental organizations in the state of Indiana. These organizations will likely find our data useful for future community planning.

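### Daily severity has no stated common unit in STRIVE and DISE, which can create a difference by arithmetic, and the named ANOVA cannot show whether the two tools agree

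*Protocol article*

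**What the plan says.** **STRIVE.** Under Measurement of Stress With the STRIVE App, the protocol article says: "When participants experience a daily stressor, they are asked to open the app and provide a rating of their stress level". Each app report therefore carries its own rating, on a 7-point scale according to Table 2.

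**Modified DISE.** Under Measurement of Stress With the Modified DISE Tool, the evening survey covers "the number of times participants felt stressed over the course of the day, their overall stress level", and then "questions about specific stressor categories (eg, had an argument and had work stress) and how stressful each of those experiences was for the participant". Table 2 lists the severity item as "Self-reported stress level by stressor (7-point scale". The same Methods section says the tool was adapted so that it could be compared directly with STRIVE.

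**Comparison.** Under Comparison of STRIVE and DISE Stressor Data, one of the outcomes is "the average subjective severity of stressors per day". Stressors from both tools are coded into 7 DISE categories. The named analysis is a repeated measures ANOVA with a tool-by-mode interaction, an order factor and demographic adjustment.

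**Aim and hypothesis.** The Introduction sets out to learn "how EMA measurement of daily stress is similar to and different from a modified version" of the DISE. The Results section predicts that with STRIVE "midlife adults will report a greater number of daily stressors, a lower average stressor severity, and different types of stressors".

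**The concern.** The severity outcome is a mean, and its value depends on what is averaged. If STRIVE averages over events and DISE over categories, three minor work stressors enter the STRIVE mean three times and the DISE mean once. Participants who live through the same day and rate it in the same way could then show different severity in the two tools. A lower STRIVE mean would be hard to interpret: it could reflect the unit of averaging, the capture of more minor stressors, or a lower rating of the same stressor.

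The second issue is separate. The aim asks about similarity, but a test of mean differences does not address it. Two tools can have equal daily means while recording quite different stressors. The week of concurrent use yields same-day pairs that could settle this: at most 150 participants x 7 days = 1,050 pairs with full compliance. The section on the comparison names no agreement measure for them.

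**Working it through.** The article gives no effect size, SD, power or event rate for this comparison, so there is no figure of the plan to reproduce. The check applies two summaries to the same events with the same ratings, so that any gap comes from the unit alone.

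**Definitions, per day**
- STRIVE = sum of event ratings / number of events.
- DISE, typical-event rule = mean over categories of the category's mean rating.
- DISE, worst-event rule = mean over categories of the category's highest rating.

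**Worked days**
- Work stress 2, 2, 5 and argument 5. STRIVE = 14/4 = 3.5. DISE = (3 + 5)/2 = 4.0 (typical) or (5 + 5)/2 = 5.0 (worst).
- Work stress 6, 6, 6 and argument 2. STRIVE = 20/4 = 5.0. DISE = (6 + 2)/2 = 4.0 under either rule, so the sign reverses.

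**Simulation.** From the article: 7 categories and a 7-point scale. Assumed: category weights 0.30, 0.25, 0.20, 0.05, 0.08, 0.07, 0.05; Poisson events with mean 0.5 to 4 per day; days with no event dropped; ratings normal with mean 3.5 and SD 1.4, rounded and limited to 1-7; 30,000 days per scenario. In two of the three settings the category mean moves by 0.7 points per SD of category weight, so that frequent categories are milder or more severe.

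DISE minus STRIVE, typical-event rule / worst-event rule:

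| Mean events per day | No link | Frequent categories milder | Frequent categories more severe |
|---|---|---|---|
| 0.5 | 0.00 / +0.04 | 0.00 / +0.04 | 0.00 / +0.04 |
| 1 | 0.00 / +0.08 | +0.01 / +0.08 | -0.01 / +0.07 |
| 2 | 0.00 / +0.16 | +0.02 / +0.17 | -0.02 / +0.14 |
| 4 | 0.00 / +0.31 | +0.06 / +0.34 | -0.06 / +0.24 |

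The gap arises only on days with repeat events in one category: about 6% of stressor days at 0.5 events per day and 66% at 4.

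**Counts.** With no link, counting categories in DISE would give 1.21 against 1.28 STRIVE events per stressor day at the lowest rate, and 2.81 against 4.06 at the highest. This applies only if categories are what is counted.

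**Capture against rating.** Take events 2, 2, 5, 5 and suppose only the two 5s are recalled in the evening. STRIVE = 14/4 = 3.5 and DISE = 10/2 = 5.0, although each stressor reported in both is rated identically. A comparison of daily means cannot separate this from a lower rating of the same event.

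**Agreement.** 150 pairs with equal means and SD 1 were drawn 2,000 times, with a paired t test at 5% standing in for the mean comparison. Rejection rates were 0.0615, 0.055 and 0.047 at correlations 0, 0.5 and 0.95. A non-significant result is about equally likely whether the tools are unrelated or almost interchangeable.

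**The case against.** The strongest reply is that the article never says DISE severity is averaged over categories. Table 2 says by stressor, the items are not shown, and the tool was adapted for direct comparison. This stands as a caution: category-level rating is the natural reading of the text, but an inference. A shared 7-point scale does not by itself give a shared unit, however, and the comparison section leaves the average undefined.

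A reader might go further and infer that the design builds in its own hypothesised result. The documents do not support that. The consistent positive sign depends on assuming that a category rating reflects the worst event; under a typical-event rule the gap is near zero or reversed. Nor is the count prediction necessarily affected, because the DISE has a separate item on how often stress was felt, although the comparison section does not say which count is used. One might also suppose that events after the evening survey tilt the result, but no completion time is given and the effect was not quantified.

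It is also fair to say that capturing more minor stressors is a real difference between tools and fits the prediction, which does not claim that the same stressor is rated lower. That stands, and is a reason to report the two separately.

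Finally, a condensed article may leave agreement measures to a fuller plan, and nowhere does it say that a null ANOVA will be read as similarity. It cannot be concluded that the concurrent pairs will go unused. What remains is that the method the article does name cannot answer the similarity half of its own objective.

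**Conclusion.** The point holds in a conditional form. The daily severity average has no stated common unit, and on the natural reading the two tools use different ones. If repeat events in a category share one DISE rating, identical experience can shift DISE minus STRIVE by about +0.04 to +0.34 points (worst-event rule, the hypothesised direction) or about -0.06 to +0.06 (typical-event rule). These sizes rest on assumed event rates, category weights and ratings. With no SD in the article, their weight relative to a true difference cannot be judged.

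The similarity point does not depend on those assumptions: a comparison of means cannot establish agreement. Neither point invalidates the study. Both limit what its third aim can claim, and both can be remedied cheaply.

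**What to change.** In Comparison of STRIVE and DISE Stressor Data:

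1. State from the actual DISE items whether repeat events in a category are rated once or separately.
2. Collapse STRIVE events to the 7 DISE categories per day before averaging severity, and report both the peak and the mean within category. If the DISE does rate repeats separately, collapse it in the same way.
3. Name the DISE item on how often stress was felt as the source for the count comparison.
4. For the concurrent week, add same-day agreement: limits of agreement for counts, kappa for each category, and the severity difference on stressors matched by day and category.
5. Base any claim that the tools are similar, or that the same stressor is rated lower in STRIVE, on these analyses and not on the ANOVA.

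The cost is extra analysis of data already collected; the coding into 7 categories is planned anyway. The severity difference may shrink once the unit is common.

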### Geospatial Analysis

We will fit spatiotemporal regression models to determine the impact of specific elements of the built and natural environment on daily stressors. Given the nature of our spatially dependent data, traditional regression-based approaches (eg, Poisson or negative binomial regression) violate the independence assumption required for generalized linear models. Ignoring the dependence of spatial data can underestimate standard errors, resulting in overly narrow confidence interval estimates and, consequently, incorrect statistical inference [44]. Thus, we will use spatiotemporal models that can simultaneously account for dependence (autocorrelation) in geospatial locations and temporal measurements. We will do this using Integrated Nested Laplace Approximation (INLA) models. Specifically, we will fit zero-inflated negative binomial INLA models, as these models can account for the many instances where stress experiences are not recorded (zero inflation) while still adjusting for the spatial and temporal autocorrelation of each measurement [45,46]. Importantly, the INLA modeling approach is robust as it can incorporate individual-level characteristics and group-level (ie, neighborhood) characteristics while adjusting for the spatial and temporal autocorrelation [47]. INLA uses a Bayesian paradigm, can fit offsets for any necessary weightings (eg, population size or number of measurements), is able to handle both point process (ie, singular latitude and longitude locations) and irregular lattice data (ie, polygons of parks and census tracts), and can analyze the individual impact of temporal, spatial, and spatiotemporal effects [46]. Through this analysis, we can identify the magnitude, direction, and impact of participant attributes (including data collected through the pretest survey and real-time collection of heart rate and activity level data from the Polar Unite watch), neighborhood features, and location characteristics on daily stressors.

### Qualitative Analysis of Reported Stressors

We will conduct an analysis of data reported through the STRIVE app in a 2-step process including open and axial coding [48]. Open coding will be conducted twice: first to code stressors into stressor types and second to code mentions of elements of the built and natural environment that played a role in the stressful experience. This open coding process will be conducted on qualitative responses to the question, “Please discuss what is causing you stress.” In this open coding process, researchers will be versed in previous research categorizing daily stressors to identify themes in the data that may overlap with commonly experienced daily stressors identified in previous research [49]. Any new themes that emerge will be given new names and detailed descriptions. In the second axial coding step, researchers will analyze stressor and environmental characteristic themes to look for those that may be related to identify linkages, creating meta-categories for daily stressors that may be similar in nature. Then, the open and axial coding processes will be conducted on participant photographs that accompany stressor reports. Characteristics of the environment in which stress occurs will be coded for each participant photograph, allowing for triangulation among themes generated by text-based responses and participant photographs**.** This data triangulation will allow us to understand how daily stressors are related to specific elements of the built and natural environment.

### Comparison of STRIVE and DISE Stressor Data

We will compare the number of stressors reported, the type of stressors reported, and the subjective severity of stressors reported by the same individual using the DISE and STRIVE app across 3 time periods. The 3 time periods are designed to differentiate between stand-alone use of each instrument and concurrent use of both instruments, as there is potential for these instruments to be complementary in terms of the scope and depth of data captured. Thematic coding of stressors reported through the DISE and STRIVE app will be conducted to allow for comparison between the two. All stressors will be coded into 7 categories specified by the DISE to retain consistency. Stressful events are categorized into 1 of 7 broad classifications organized by interpersonal tensions, work or education, home, finances, health or accident, network, and miscellaneous. As the unit of analysis of the DISE is the “day,” we will conduct a repeated measures ANOVA to compare the number of stressors reported per day, the average subjective severity of stressors per day, and the type of stressors reported per day across the 3 modes of daily stress reporting, including an interaction of group (STRIVE or DISE) and mode (using only one or both together) to test if there is any effect on the reported stressors by use. A factor will also be included for the order receiving the conditions to account for carryover effects. Models will also be adjusted by demographic variables.

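### The seven shared labels do not separate who classified a stressor from which tool captured it, so a difference in stressor types cannot be read purely as different capture

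*Protocol article*

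**What the plan says.** All references are to the Protocol article.

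- **DISE.** Table 2 lists, for the end-of-day measure, "Self-reported stressor type Self-reported stress level by stressor (7-point scale". The section on the modified DISE describes "questions about specific stressor categories (eg, had an argument and had work stress", each rated for how stressful it was. No DISE text item is listed.
- **STRIVE.** Table 2 lists "Self-reported stressor (text-based". The qualitative analysis section has researchers open-code the answers to the app's open question, "first to code stressors into stressor types". No participant-chosen category is listed.
- **Comparison.** The section on comparing the two tools says "Thematic coding of stressors reported through the DISE and STRIVE app will be conducted to allow for comparison between the two", and then "All stressors will be coded into 7 categories specified by the DISE to retain consistency". It plans a repeated measures ANOVA with a group (STRIVE or DISE) by mode interaction, an order factor and demographic adjustment.
- **Purpose of the modification.** "The DISE was modified to allow for direct comparisons between STRIVE and DISE".
- **Hypothesis.** The third expected finding is that, on STRIVE compared with the DISE, "midlife adults will report a greater number of daily stressors, a lower average stressor severity, and different types of stressors".

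**The concern.** Sharing seven labels harmonises the vocabulary. It does not harmonise the act of classification. On the listed measures, a DISE stressor carries the category the participant gave when answering a preset question. A STRIVE stressor carries the category a researcher inferred from the participant's text. The same event can receive different labels for that reason alone.

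At stake is one of the three components of the third hypothesis. A finding of different types would naturally be reported as real-time assessment picking up kinds of stressors that evening recall misses. The plan as described cannot tell that apart from researchers and participants sorting the same events differently. A larger sample or another test would not help, because the confounding lies in the measurement.

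**Working it through.** The article states no alpha, power, effect size or coder agreement for this comparison, so there is no plan figure to reproduce. Two checks were made.

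**1. Can the planned terms separate classifier from instrument?** There are four report streams. Code instrument (STRIVE = 1), both tools in use = 1, their product, and classifier (researcher from text = 1):

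| Stream | Intercept | Instrument | Both | Instrument × both | Classifier |
|---|---|---|---|---|---|
| DISE, alone | 1 | 0 | 0 | 0 | 0 |
| DISE, combined week | 1 | 0 | 1 | 0 | 0 |
| STRIVE, combined week | 1 | 1 | 1 | 1 | 1 |
| STRIVE, alone | 1 | 1 | 0 | 0 | 1 |

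The classifier column equals the instrument column. The rank is 4 without it and 4 with it, so its effect cannot be estimated. Order and demographics do not vary between tools within a participant's combined week, so they do not break the alias. If STRIVE reports also carried a participant-chosen category, two further streams would have instrument = 1 and classifier = 0, and the rank would be 5 of 5.

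**2. How large could the artefact be?** All inputs here are assumptions. True shares, identical for both tools: interpersonal 30%, work 25%, home 15%, finances 5%, health 5%, network 10%, miscellaneous 10%. Only the STRIVE side is miscoded.

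- Share *e* sent to miscellaneous: q = p(1 − e) for the other six, and q_misc = p_misc + e(1 − p_misc). With e = 10%: 0.10 + 0.10 × 0.90 = 0.19.
- Share *e* spread evenly over the other six categories: q = p(1 − e) + e(1 − p)/6. With e = 10%, interpersonal is 0.30 × 0.90 + 0.10 × 0.70/6 = 0.282.
- With n stressors per tool and m = (p + q)/2, the noncentrality is λ = n Σ[(p − m)² + (q − m)²]/m. Rejection is the noncentral chi-square tail (6 df) beyond 12.59, the 5% critical value.

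| STRIVE miscoding (assumed) | λ, n = 500 | Rejects | λ, n = 1,000 | Rejects |
|---|---|---|---|---|
| 5% spread evenly | 0.42 | 7% | 0.84 | 9% |
| 10% spread evenly | 1.63 | 13% | 3.26 | 22% |
| 2% to miscellaneous | 0.83 | 9% | 1.67 | 13% |
| 10% to miscellaneous | 16.3 | 88% | 32.7 | 99.7% |
| 5% to miscellaneous, and 20% of interpersonal coded as work | 11.1 | 70% | 22.2 | 96% |

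This treats stressors as independent, whereas the plan analyses days within participants. A paired simulation is closer to the plan. It used 150 participants, one DISE-only and one STRIVE-only week of 7 days, 0.5 to 1 stressor per day, shares 25/25/18/8/8/8/8% and a paired t-test at 5%. The pattern was the same:

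- 5% sent to miscellaneous moves that share from 8% to 12.6%, and a false difference is declared in 64% to 90% of runs.
- 10% sent to miscellaneous gives 17.2%, and a false difference in 99% to 100% of runs.
- Even miscoding, judged on the work category, gives about 5% at 5% miscoding, 6% to 8% at 10%, 13% to 21% at 20% and 22% to 44% at 30%.
- With no miscoding the rate is about 4% to 6%.

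**The case against.** The strongest reply is that the plan codes stressors from both instruments, in the sentence just before the seven categories are introduced, and that the DISE was modified with comparability in mind. That stands as a description of the plan. A reader might infer that only STRIVE is researcher-coded, and the article does not support that. It does not remove the alias, though: with no DISE text listed, a coder has only the participant's category to work from. The full protocol could contain a DISE text field, and if it does, the point weakens accordingly.

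Other stronger readings also lack support:

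- **One code against many.** A reader might infer that DISE events can count under several categories while STRIVE events get one. The one-of-seven rule is stated for stressful events generally, and no different rule is given for the DISE.
- **Unmasked coders.** The article is silent on masking. Coder procedure is commonly left to the full protocol, so silence is not evidence of a fault.
- **Tick-box answers, or vague texts defaulting to miscellaneous.** Neither is stated.
- **A false finding is near certain.** That holds only for sizeable directional miscoding. Small or evenly spread miscoding leaves the error rate much closer to nominal.

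It can also be said that response format is part of what the third aim compares. That is fair for a comparison of the tools as packages. But the hypothesis concerns what adults report, and a researcher's coding decision is not part of their report.

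**Conclusion.** The point holds in limited form. On the measures the article lists, classifier and instrument are fully aliased in every week, and none of the planned model terms separates them. A type difference is therefore evidence of different capture or different classification, not of capture alone. The statement that common coding retains consistency is true of the labels only.

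The size is not known. Under the assumptions above, the rejection rate with identical events runs from about 7% to 99.7%, depending mainly on whether miscoding is spread out or directional. The documents do not say which applies, and that is the reason to measure it. The case rests on the listed measures being complete for stressor type. It concerns one of three outcomes in one of three aims of a stage 0 study. It does not rest on the seven-category alias for the number of stressors or their severity, which are not assessed here.

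**What to change.** Three steps, using data the study already collects:

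1. Code STRIVE texts with study week and DISE answers masked, and say so. This does not break the alias, but it stops the coder's expectations from adding to it.
2. In the combined week, on days with exactly one STRIVE report and one DISE stressor, cross-tabulate coder category against participant category. Report the agreement beside the type comparison.
3. State in advance that a type difference will be interpreted as different capture only if it is larger than, or in a different direction from, what that disagreement table could produce. Otherwise describe it as a difference in capture or classification.

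The cost is analysis time. There is also a limit: matched days are a subset, and the two reports may concern different events. The table should be read as a lower bound on agreement, so step 3 is cautious and may leave a real difference labelled ambiguous. For the same reason the table should not be used to correct the STRIVE distribution, since that could remove a true difference.

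Adding a participant-chosen category to the app would make the classifier estimable (rank 5 of 5), but it is optional. It would bring DISE categories into the STRIVE-only week and may prime participants, it adds input to an app kept deliberately brief, and it would change the instrument after enrollment began in August 2023.

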**Figure 1 figure1:**
[figure not shown]
The Stress Reports in Variable Environments (STRIVE) app.

We have created a protocol to promote the safety of research participants during their reporting of daily stressors with the STRIVE app. If they cognitively appraise themselves as stressed and are in a situation in which it is unsafe to use their phones (eg, driving a car), they are asked to proceed to the nearest safe location before recording their experience. Participants will be asked to indicate when and where the stressor occurred if they are not reporting from the location in which the stress occurred in their later description of it. Many people go through a day without experiencing a stressor [43]; for days when this is the case, participants will be asked to indicate on their app that they had not experienced stress but were still actively participating in the study.

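### The planned daily mean severity has no value on stressor-free days, so a day-level repeated measures ANOVA does not suit the STRIVE versus DISE severity comparison

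*Protocol article*

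**What the plan says.** The section Comparison of STRIVE and DISE Stressor Data takes the day as unit because that is the unit of the DISE. It then says "we will conduct a repeated measures ANOVA to compare the number of stressors reported per day", and in the same sentence names "the average subjective severity of stressors per day" and the type of stressor as further outcomes. The model has tool and mode terms, an order factor and demographic adjustment.

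The section Measurement of Stress With the STRIVE App says "Many people go through a day without experiencing a stressor". On such days "participants will be asked to indicate on their app that they had not experienced stress but were still actively participating in the study". A stressor-free day is therefore an observed day, not a missing one.

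The third expected finding in Results is that with STRIVE, compared with DISE, "midlife adults will report a greater number of daily stressors, a lower average stressor severity, and different types of stressors". Geospatial Analysis provides for excess zeros through a zero-inflated model. The STRIVE versus DISE comparison has no corresponding provision.

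**The concern.** A count of stressors is 0 on an empty day, which is a valid value. A mean severity over no stressors has no value. The outcome and the unit that the article fixes are therefore incompatible on days that it expects from fully compliant participants.

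The analyst must then do one of two things:

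- Leave those days out. The repeated measures layout then has holes, and people with no stressor in a week may drop out of the within-person contrast.
- Give the days the value 0. The outcome then becomes roughly the share of days with a stressor times their mean severity, so a tool that records more stressors can look more severe for that reason alone.

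Lower average severity is one of three hypothesised differences between the tools. Its precision, the people it describes and, in some circumstances, its sign depend on this choice.

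**Working it through.** **No figure to reproduce.** The article gives no effect size, stressor rate, share of empty days or capture rate for this comparison. The rates below are assumptions. From the article come the 150 participants, the one-week periods and the 7-point scales (coded 1 to 7 by assumption).

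**Formulas.** Let m be the mean severity of the stressors a tool records, n the mean number it records per day, and p0 the share of days with none. With Poisson counts p0 = exp(-n), and with severity unrelated to the day's count:
- empty days dropped: difference = mS - mD
- empty days scored 0: difference = mS(1 - p0S) - mD(1 - p0D)

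If STRIVE is lower when empty days are dropped, the signs are opposite only if 1 < mD/mS < (1 - p0S)/(1 - p0D).

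**Worked example.** Both tools give a shared stressor the same rating. There is 1 stressor per day, and severities 1 to 7 have shares 5, 10, 20, 30, 20, 10 and 5% (mean 4.00, variance 2.1). STRIVE captures all; DISE capture rises linearly from 0.3 at severity 1 to 1 at severity 7 (average 0.65).
- mS = 4.00; mD = 4 + (0.7/6)(2.1)/0.65 = 4.38
- p0S = exp(-1) = 0.37; p0D = exp(-0.65) = 0.52
- dropped: 4.00 - 4.38 = -0.38
- scored 0: 4.00 × 0.632 - 4.38 × 0.478 = 2.53 - 2.09 = +0.44
- condition: 4.38/4.00 = 1.09, below 0.632/0.478 = 1.32, so the sign reverses

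**Where the reversal stops.** At 5 stressors per day in the same example, the zero-scored means are 3.97 and 4.21. Their difference is -0.23 before rounding, the same direction as dropping. A grid over three severity distributions and three rules by which DISE selectively misses milder stressors gave:

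| Stressors per day | STRIVE empty days | Opposite signs |
|---|---|---|
| 0.25 to 1 | 37% or more | 26 of 27 (one essentially zero) |
| 2 | 14% | 6 of 9 |
| 3 | 5% | 2 of 9 (both near zero) |
| 5 | 1% | 0 of 9 |

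With non-selective 70% DISE recall there was no reversal in 18 scenarios. Dropping then gives 0, and scoring 0 gives +0.07 to +0.51. If both tools capture the same stressors, both differences are 0.

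A second set let STRIVE miss stressors too, with DISE capture 0.35 + 0.08 × severity. With STRIVE capture 0.85, the results at 0.5 to 2.5 stressors per day were -0.26 dropped and +0.06 to +0.17 scored 0. There was no reversal at 4 per day, and none with STRIVE capture 0.70, which is close to the DISE average of 0.35 + 0.08 × 4 = 0.67. The reversal therefore also needs one tool to capture clearly more.

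**Loss under dropping.** In that second set, at 0.5 to 1.5 stressors per day and with rates varying between people, at most 7% of people had a defined value on all 14 days of the two single-tool weeks. Between 68% and 94% had at least one defined day in each week.

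**At the trial's size.** A simulation of 150 people with 7 days per tool, the worked example's type of recall and strong between-person variation had 53% and 64% empty days. Dropping gave -0.38 (significant in 93% of runs). Scoring 0 gave +0.32 (significant in 95%). On average 119 of 150 people had a defined mean in both weeks.

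**The case against.** The strongest reply has three parts.

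- **Level of detail.** This is a condensed article, and the handling of empty days in a derived mean could sit in a fuller plan.
- **Zero scoring is not proposed.** The outcome is severity of stressors, the DISE rates each experience, and the hypothesis concerns average stressor severity. All of this points to severity given a stressor.
- **A lower conditional mean is not a bias here.** The hypothesis is about what people report through each tool. If STRIVE picks up extra mild stressors, lower reported severity is the predicted difference.

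The second and third parts stand. A reader might infer that the plan will score empty days 0, or that the sign of the severity result is arbitrary. The article supports neither: it never adopts zero scoring, and the reversal fails under non-selective recall, at high stressor rates, or when the tools capture similar numbers. A reader might also infer that most or many days are empty, but the article says only that many people have such a day.

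The first part stands only in part. The article itself fixes outcome, unit and model, and that combination does not suit the data it expects. Under the natural conditional reading, the repeated measures ANOVA is still the wrong tool, because it handles uneven and absent cells poorly.

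**Conclusion.** The concern holds in a limited form. The day-level mean is undefined on valid, observed days, and the named model cannot use those days. On the reading the text favours, the cost is lost days or people; its size depends on stressor rates that the article does not give, and the figures above are illustrations over an assumed range. The sign reversal is a conditional risk of one convention, not a property of the plan as written.

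A separate limit on interpretation remains. Even with empty days dropped, STRIVE can show lower severity with identical ratings of shared stressors, purely through capture. That answers the stated hypothesis about reported stressors, but it should not be read as people rating the same stressor lower. The point merits a change before analysis. It does not threaten the study's design or the count comparison.

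**What to change.** 1. State that stressor-free days carry no severity value and are never scored 0.
2. Replace the day-level ANOVA for severity with a mixed model on each reported stressor, with random effects for participant and participant-day, keeping the planned tool, mode, order and demographic terms. People with empty days or an empty week then still contribute the stressors they report.
3. Describe the result as severity of the stressors each tool captured, and read it beside the count result. The mixed model alone does not remove the capture effect.
4. As a secondary analysis, in the week when both tools are used, compare severity only on person-days and DISE categories that both tools reported. This separates rating from capture and uses the concurrent week and the seven-category coding already planned.

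The cost is a rewritten analysis paragraph and one added secondary analysis, with no new data. The matched comparison uses fewer records, so its interval is wider, and it speaks only to concurrent use.
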